### Randomization and Follow-Up

Eligible men will be randomized using a 1:1 allocation ratio to the intervention and control groups. Randomization lists for each study site have been pregenerated by researchers. Each envelope with a unique number will be assigned for 1 allocation sequence, into which a card with grouping information will be put before sealing. Trained investigators at each study site will assign an envelope to each participant according to the order of the participant’s arrival. Participants cannot be blinded due to the nature of the intervention. After randomization, trained researchers will provide HIV prevention counseling to participants in both groups, including promotion of consistent condom use and regular HIV testing.

Participants randomized to the intervention group will be encouraged to complete VMMC within 1 week of enrollment. Time to VMMC can be extended up to 3 months after enrollment on a case-by-case basis. We recommend participants to undergo VMMC at a secondary or higher-level medical center of their own choice. Although the clinical VMMC activities are not part of study procedures, a research assistant would accompany the participants to the hospital to undergo the circumcision. This trial will provide a surgical subsidy of CNY 1000 (US $160). If participants do not complete VMMC within 1 month of enrollment, a text message reminder will be sent. The surgeon will check the condition of the foreskin of participants before the operation to determine if surgery is necessary. Men in the intervention group will be advised to abstain from sex for 6 weeks after undergoing VMMC, and the 12-month follow-up period will begin after this 6-week period of abstinence. If men resume sexual behaviors earlier than 6 weeks after VMMC, then the 12-month follow-up period will begin at the time of their first sexual encounter after VMMC.

Men randomized to the control group will complete the baseline survey after enrollment. The 12-month follow-up period for the control group will begin immediately after completing the baseline survey. At the end of the 12-month follow up period, men in the control group will be offered a CNY 1000 (US $160) subsidy to undergo VMMC.

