### Sample Size

The sample size is calculated based on the supposed protective rate of circumcision. Studies have shown that HIV incidence among MSM was 12.5/100 person-years in Chongqing [26], 15.5/100 [27] and 10.3/100 person-years [28] in Shenyang, and 15.6/100 person-years in 8 cities in China [29]. Considering participants in the CoM Study predominantly practiced insertive anal sex, consequently with lower HIV infection risk compared with those who primarily practiced receptive role, and that the effect of VMMC may be higher among men who primarily or exclusively practice the insertive anal intercourse than MSM overall, we suppose HIV incidence among MSM to be 10/100 person-years and protective rate of circumcision to be 80%, and thus, HIV incidence would be 2/100 person-years in the intervention group. A target sample size of 240 (120 in each group) is set to achieve 80% power at 1-sided α=.10, with 10% lost to follow-up.

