### Statistical Analysis

All data will be analyzed based on the principle of intention to treat. We will assess the type of missing data and assess attrition effects by testing whether there are systematic differences between dropouts and nondropouts. Key baseline characteristics will be examined between the intervention and control groups to ensure they are balanced; if not, subsequent analyses will assess whether these characteristics are confounding factors of the intervention.

For continuous variables, we will calculate means and SDs, and means will be compared with 2-sample *t* tests or Mann-Whitney tests. For categorical variables, proportions will be compared with chi-square tests or Fisher exact tests. In addition, we assume that HIV status at the end of follow-ups is grouped censored data and suitable for exponential, proportional hazards model with constant baseline hazard. Therefore, differences between the intervention and the control groups will be identified with a Poisson regression model, which includes observed covariates (ie, HIV risk behaviors, such as condom use, number of sexual partners, frequency of insertive anal sex, and HIV-positive sexual partners as well as demographic variables, such as age, education level, and income). Incidence rates will be calculated for each outcome in the 2 groups. Moreover, the incidence rate ratios and their 95% CIs will be estimated using the Poisson regression model. For all the outcome variables, including the primary (ie, HIV incidence) and secondary (ie, penile HPV incidence, clearance and persistent infection, HSV-2 incidence, and syphilis incidence) outcomes of interest, the aforementioned analyses will be repeated across all the visits (ie, 6- and 12-months follow-ups).

The changes in sexual behaviors after VMMC over time between the intervention and the control groups will be compared with the generalized estimating equations. For outcomes of VMMC safety and satisfaction among circumcised MSM, we will perform the same statistical description and comparative analyses described as above.

A 2-sided *P* value lower than .05 will be used to infer statistically significant difference. All the statistical analyses will be performed with R software (version 4.2.1; R Core Team).

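### The sample size uses the effect of being circumcised as the effect of being assigned to VMMC, so the stated 80% power under intention to treat requires near-complete surgery uptake

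*Protocol article*

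**What the plan says.** Under Sample Size, the protocol article states its basis: "The sample size is calculated based on the supposed protective rate of circumcision". For the control rate, "we suppose HIV incidence among MSM to be 10/100 person-years". It then sets the "protective rate of circumcision to be 80%, and thus, HIV incidence would be 2/100 person-years in the intervention group". The target is 240 men, 120 per group, "to achieve 80% power at 1-sided α=.10", and the one inflation named is "with 10% lost to follow-up".

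Under Statistical Analysis: "All data will be analyzed based on the principle of intention to treat". The comparison is a Poisson regression, judged at 2-sided .05.

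Under Interventions and Randomization and Follow-Up, surgery comes after randomization, ideally within a week and at most 3 months later, at a hospital the man chooses. "If participants do not complete VMMC within 1 month of enrollment, a text message reminder will be sent". The surgeon checks beforehand whether the operation is needed. The intervention group's 12 months start after surgery, at 6 weeks or at first sex if that is earlier. The Table 2 footnote says that intervention men are formally enrolled once the circumcision is done.

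**The concern.** An 80% reduction from circumcision becomes a rate of 2/100 person-years in the assigned group only if every assigned man is operated. Under intention to treat, a man who is followed but not operated stays in the VMMC group and contributes roughly the control rate. Loss to follow-up is a different matter: it removes person-time but does not dilute the contrast.

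Few events are expected, about 11 in the control group and 2 in the VMMC group, so one additional VMMC-group infection matters. If uptake falls short of near-complete, a null result would be read against a power that the intention-to-treat comparison did not have.

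**Working it through.** **Inputs from the documents.** Control rate 0.10 per person-year, intervention rate 0.02, 120 men per arm, 10% lost, 12 months of follow-up, 1-sided α = .10, power 80%. Evaluable person-time is taken as 120 × 0.9 = 108 person-years per arm, a simplification that ignores partial follow-up. **Assumed, because the documents give no figure:** the unoperated share u, varied from 0 to 20%. Unoperated men are given the control rate, and no control man is circumcised before month 12.

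**1. Reproducing 240.** The article names no formula. With the log rate ratio:

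n = (1.2816 + 0.8416)² × (1/0.10 + 1/0.02) / (ln 0.2)² = 4.508 × 60 / 2.590 = 104.4, so 105 person-years per arm.

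105/0.9 = 116.7, so 117 per arm and 234 in total, within 3% of 240. At the same 1-sided .10, a pooled two-proportion formula gives 79, or 88 per arm after inflation. With a continuity correction it gives 103, or 115 per arm. If α = .10 is read as 2-sided, the pooled two-proportion formula gives 108, and 108/0.9 = 120 exactly. The two versions that come nearest (log rate ratio at 1-sided .10, pooled two-proportion at 2-sided .10) both use 2/100 for the whole intervention group and inflate only for loss.

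**2. Intention-to-treat rate.** Rate ratio RR = 0.2(1 − u) + u; group rate = 10 × RR per 100 person-years.

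**3. Power at 108 person-years per arm, 1-sided .10.** For the log rate ratio, power = Φ(|ln RR| / √(1/10.8 + 1/(10.8 RR)) − 1.2816).

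- u = 0: 1.609/0.745 = 2.159; Φ(0.878) = 81%.
- u = 0.10: 1.273/0.651 = 1.957; Φ(0.675) = 75%.

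| Unoperated | Rate per 100 py | RR | Log rate ratio | Exact conditional | Pooled two-proportion |
|---|---|---|---|---|---|
| 0% | 2.0 | 0.20 | 81% | 83% | 89% |
| 5% | 2.4 | 0.24 | 78% | 78% | 85% |
| 10% | 2.8 | 0.28 | 75% | 73% | 81% |
| 15% | 3.2 | 0.32 | 71% | 67% | 77% |
| 20% | 3.6 | 0.36 | 67% | 62% | 72% |

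**4. Where power crosses 80%.** At u = 2.0% (log rate ratio), 3.4% (exact) and 11.6% (two-proportion), that is, at uptake of about 98%, 97% and 88%. With α = .10 read as 2-sided, the pooled test has 80.0% at full uptake and no margin at all.

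**5. At the level in Statistical Analysis, 2-sided .05.** The log rate ratio formula gives Φ(2.159 − 1.960) = 58% at full uptake and Φ(1.957 − 1.960) = 50% at 90% uptake.

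**6. If unoperated men contributed no person-time.** RR stays at 0.20 and the VMMC arm shrinks to 108(1 − u) person-years. At u = 0.10 that is 97.2 person-years and 1.944 expected events: 1.609/√(1/10.8 + 1/1.944) = 2.066, and Φ(0.784) = 78%. At u = 0.05 power is 79.7%.

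**The case against.** The strongest reply is that unoperated men may never be counted. The Table 2 footnote enrols intervention men formally only after the operation, and the follow-up clock in Randomization and Follow-Up starts only after it, so an unoperated man has no defined start. On that reading 2/100 holds for the men who are followed. But it drops randomized men from one arm only, which contradicts the intention-to-treat statement, and power still falls just below 80% by 5% unoperated (step 6). It exposes a contradiction to be resolved and does not rescue the power figure.

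The second reply is that uptake may well be high. Willingness to undergo VMMC and a foreskin covering over half the glans are entry criteria, there is a CNY 1000 subsidy, and a research assistant goes with the man to hospital. This stands. A reader might infer from the reminder that the protocol expects many men to go without surgery. It does not show that: the reminder falls at 1 month inside a 3-month window, so it points to delay more than to non-completion. The surgeon's check leaves non-completion possible, but no passage says how common it will be.

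Third, the tolerance depends on the formula, which the article does not name. That also stands. The most forgiving version allows nearly 12% unoperated, but it would have needed only 88 per arm and so is unlikely to be the source of 240.

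**Conclusion.** The point holds as a mismatch between the planning effect and the planned analysis. Sample Size treats the effect of circumcision as the effect of assignment and makes no allowance for men assigned to VMMC but not operated. At 1-sided .10 the stated 80% therefore rests on uptake of about 97% to 98% with the two rate-based tests. The loss is about 3 points at 5% unoperated, 6 at 10% and 14 at 20% with the log rate ratio. These sizes rest on the assumed uptake range, on the control rate in unoperated men, and on the article's own 10/100 and 80%.

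Two stronger conclusions are not supported. A reader might infer that 240 is an arithmetic error; it follows closely from its inputs. A reader might also infer that the trial is known to fall short of 80% because of non-uptake; without an uptake figure that cannot be said. The gap between 1-sided .10 in Sample Size and 2-sided .05 in Statistical Analysis costs more power (81% to 58% at full uptake) but is a separate matter. It is relevant here only because a restated power means little without its significance level.

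**What to change.** In Sample Size:

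- Describe 80% as the assumed effect in operated men and state an expected uptake.
- Derive the intention-to-treat rate as 10 × [0.2 × uptake + (1 − uptake)] per 100 person-years, for example 2.8 at 90% uptake.
- Restate power over a short uptake range, naming the formula and giving the significance level with every figure. At 90% uptake the log rate ratio formula gives about 75% at 1-sided .10 and about 50% at 2-sided .05.

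Separately, reconcile the Table 2 footnote on formal enrolment and the follow-up start in Randomization and Follow-Up with the intention-to-treat statement, so that it is clear that men randomized to VMMC but not operated are followed and counted in the intervention group.

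The cost is one rewritten paragraph, a reconciled footnote and start rule, and a less favourable stated power. Recruitment ran through July 2022 and the enrolled number stays as it is; the gain is that the result will be read against an honest power figure.

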Sexual position preference may have a significant impact on the efficacy of VMMC to reduce HIV infection among MSM. Men who practice insertive anal sex may benefit more from VMMC than those who practice receptive anal sex. Subanalysis in a 2019 systematic review and meta-analysis [15] found that MSM who primarily engage in insertive anal sex had a 56% lower odds of HIV infection, a stronger association compared to what was found among MSM overall. In China, 70% of MSM practice either exclusively insertive anal sex or both insertive and receptive anal sex [17,18]. Thus, VMMC has the potential to become an important HIV prevention option for most MSM in China.

Only 15.3% of MSM in China have undergone circumcision [19]. This proportion is lower than the global average of 37%-39% [20]. Mainstream social conventions and religious practice in China are neutral on circumcision, neither promoting nor forbidding the procedure. Implementing a VMMC intervention in China should not be significantly hindered by Chinese traditions or cultural values. Other potentially effective interventions, such as PrEP, are still in promotion phase in China, which is impeded by high cost, low accessibility, and stigma among MSM [21,22]. As for consistent condom use, the rate of its use among MSM remains relatively low, approximately 50% [23,24]. Hence, it is essential to determine an alternative HIV prevention strategy in China. Given the high proportion of Chinese MSM who are uncircumcised and the need for alternative HIV prevention strategies in China, it is theoretically feasible to conduct an RCT to evaluate the efficacy of VMMC to reduce incident HIV infection among MSM in China. This RCT could provide valuable information to inform HIV prevention policy as well as future mathematical models and additional clinical trials of VMMC.

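### The 80% power is stated for a 1-sided α of .10, but significance will be judged at 2-sided P<.05, where 240 men give about 58-70% power for the assumed effect

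*Protocol article*

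**What the plan says.** Protocol article, Sample Size: the design assumption is "we suppose HIV incidence among MSM to be 10/100 person-years and protective rate of circumcision to be 80" per cent, which gives 2 per 100 person-years in the circumcised group. The target is then stated as "240 (120 in each group) is set to achieve 80% power at 1-sided α=.10, with 10% lost to follow-up".

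Protocol article, Statistical Analysis: the groups are compared by Poisson regression, and "the incidence rate ratios and their 95% CIs will be estimated using the Poisson regression model". The decision rule is "A 2-sided *P* value lower than .05 will be used to infer statistically significant difference". That section lists HIV incidence as the primary outcome among those to be analysed this way. It sets no separate level for it.

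The article does not name the sample size formula, explain why the two levels differ, or give power at 2-sided .05.

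**The concern.** Power belongs to a particular test at a particular level. Here one comparison has two levels: 1-sided .10 for planning and 2-sided .05, equivalent to 1-sided .025 for benefit, for inference. The 80% describes a test that the Statistical Analysis section does not plan to use.

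Two things are at stake.

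- A reader who takes the trial to have an 80% chance of detecting the assumed effect at the level it reports would give a non-significant result more weight than it can bear.
- While both levels stand, a result with a 1-sided P value between .025 and .10 could be called positive by the design level and negative by the analysis rule, with the choice made after the data are seen.

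**Working it through.** **Inputs from the protocol article**

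- Rates of 0.10 and 0.02 per person-year (rate ratio 0.20), 120 men per arm, 10% loss, 80% power, 1-sided α .10 (Sample Size).
- 1:1 allocation (Randomization and Follow-Up) and 12 months of follow-up (Interventions).
- 2-sided .05 and a Poisson model (Statistical Analysis).

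Evaluable men per arm: 120 × 0.9 = 108, taken as 108 person-years, so 10.8 and 2.16 expected infections, about 13 in total. Normal quantiles: 1.2816 (1-sided .10), 1.6449 (1-sided .05), 1.9600 (2-sided .05), 0.8416 (80% power).

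**Step 1. Reproduce 240**

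*Log rate ratio (Wald), the form that matches the planned Poisson model, at the stated 1-sided .10:*

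n per arm = (1.2816 + 0.8416)² × (1/0.10 + 1/0.02) / (ln 0.2)² = 104.4, so 105. Then 105/0.9 = 116.7, so 117 per arm and 234 in total. Power at 108 per arm:

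- standard error = √[(10 + 50)/108] = 0.7454
- 1.6094/0.7454 = 2.159
- Φ(2.159 − 1.2816) = 81.0%

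This is within 3% of 240 and within about one point of 80%.

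*Pooled two proportions, no continuity correction, 10% versus 2%:*

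n per arm = [z × √(2 × 0.06 × 0.94) + 0.8416 × √(0.09 + 0.0196)]² / 0.08²

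- 1-sided .10: 78.6, so 79; with loss, 88 per arm and 176 in total
- 1-sided .05 (2-sided .10): 107.9, so 108; with loss, 120 per arm and exactly 240 in total

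With a continuity correction at 1-sided .10, the two-proportion formula gives 103 per arm before loss and 230 in total. So 240 is reachable closely at 1-sided .10 by one route and exactly at 1-sided .05 by another. The article does not say which was used.

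**Step 2. Power at 2-sided .05 with 108 per arm**

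| Method | Power |
|---|---|
| Wald, log rate ratio: Φ(2.159 − 1.960) | 57.9% |
| Exact conditional Poisson | 60.6% |
| Fisher exact | 63.6% |
| Rate difference | 67.0% |
| Poisson score test | 69.7% |
| Pooled two proportions | 69.9% |

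The log-rate-ratio and uncorrected pooled formulas, the two routes to 240 in step 1, mark the ends of this range. With no loss at all (120 per arm) they give 62% and 74%.

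**Step 3. Size needed for 80% power at 2-sided .05, with 10% loss**

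- Pooled two proportions: 138 per arm before loss, 308 in total
- Log rate ratio: 182 per arm before loss, 406 in total

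**Step 4. Methods outside the range**

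- A Poisson likelihood-ratio test gives 75.7%, still below 80%.
- The Schoenfeld approximation gives 82.6%. It does not reproduce the design (7 events, about 130 men at 1-sided .10) and is unreliable for a ratio of 0.2 with about 13 events.
- Enumerating the Wald test over Poisson counts gives 52.2%. That figure counts every sample with no infection in the circumcised arm as a failure to reject, so it is partly an artefact.

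**Step 5. Sensitivity scenario**

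The Introduction (Overview) cites a subanalysis of observational studies in which "MSM who primarily engage in insertive anal sex had a 56% lower odds of HIV infection". Treating that as a rate ratio of 0.44 is an assumption. On it, power at 2-sided .05 with 108 per arm is 25% (exact Poisson), 27% (Fisher exact) and 36% (pooled two proportions).

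**The case against.** The strongest reply is that nothing is hidden. The article prints the 1-sided .10 beside the 80%, states the 80% reduction openly as a supposition, and describes the evidence it expects as preliminary. It nowhere says that a non-significant result would count against circumcision. This limits the harm: over-reading a null result is a risk, not something the authors commit to. It does not reconcile the two levels, and no power is given for the level that will be applied.

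A reader might also infer that the printed α is wrong because the uncorrected pooled formula needs only 176 men at 1-sided .10 and yields exactly 240 at 1-sided .05. The documents do not support that. The inputs are rates per 100 person-years and the planned model is Poisson; the matching formula gives 234 men and 81.0% power at the stated 1-sided .10. Replacing the α with 1-sided .05 could introduce an error, since under the log-rate-ratio formula 240 men have only 69.7% power at that level. If the printed level is nonetheless a slip for 2-sided .10, it still differs from 2-sided .05.

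A reader might further infer that the trial's true power is 25-36%, because the cited reduction for insertive men is 56%. That figure is a reduction in odds from observational studies and was not the design assumption. An odds ratio of 0.44 at 10% control risk is a risk ratio of about 0.47, so the scenario is approximate. It has no bearing on the mismatch between levels.

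**Conclusion.** Wrong as written. The Sample Size and Statistical Analysis sections apply different significance levels to the primary comparison. At the level used for inference, the stated 240 men have about 58-70% power rather than 80%, so the chance of missing the assumed effect is roughly 30-42% rather than 20%.

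This rests on the protocol's own assumptions: 10 versus 2 per 100 person-years, 108 evaluable men per arm and one year of follow-up each. The width of the range reflects the unnamed formula. The direction does not depend on that choice, because both routes to 240 fall below 80%, even with no loss to follow-up. The finding does not extend to saying that 240 cannot be derived from the stated α.

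**What to change.** Use one significance level for the primary comparison in both sections. Which level to keep is a design choice for the investigators.

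If 2-sided .05 is kept, restate the Sample Size section along these lines: 240 men (216 evaluable) give about 58-70% power at 2-sided .05 for an 80% reduction, depending on the method. Name the formula used and confirm which α produced 240: 1-sided .10 by the log-rate-ratio formula gives 234, and 1-sided .05 by pooled proportions gives exactly 240. State that a non-significant primary result is inconclusive and will be interpreted from the confidence interval for the rate ratio.

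Optionally, add the power of about 25-36% at a rate ratio of 0.44, labelled as a sensitivity scenario based on an observational odds reduction.

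The cost is wording. Recruitment ran through July 2022, so this is a reporting correction that needs no extra participants. If 2-sided .05 is kept, the stated power becomes less favourable.

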### Statistical Analysis

All data will be analyzed based on the principle of intention to treat. We will assess the type of missing data and assess attrition effects by testing whether there are systematic differences between dropouts and nondropouts. Key baseline characteristics will be examined between the intervention and control groups to ensure they are balanced; if not, subsequent analyses will assess whether these characteristics are confounding factors of the intervention.

For continuous variables, we will calculate means and SDs, and means will be compared with 2-sample *t* tests or Mann-Whitney tests. For categorical variables, proportions will be compared with chi-square tests or Fisher exact tests. In addition, we assume that HIV status at the end of follow-ups is grouped censored data and suitable for exponential, proportional hazards model with constant baseline hazard. Therefore, differences between the intervention and the control groups will be identified with a Poisson regression model, which includes observed covariates (ie, HIV risk behaviors, such as condom use, number of sexual partners, frequency of insertive anal sex, and HIV-positive sexual partners as well as demographic variables, such as age, education level, and income). Incidence rates will be calculated for each outcome in the 2 groups. Moreover, the incidence rate ratios and their 95% CIs will be estimated using the Poisson regression model. For all the outcome variables, including the primary (ie, HIV incidence) and secondary (ie, penile HPV incidence, clearance and persistent infection, HSV-2 incidence, and syphilis incidence) outcomes of interest, the aforementioned analyses will be repeated across all the visits (ie, 6- and 12-months follow-ups).

The changes in sexual behaviors after VMMC over time between the intervention and the control groups will be compared with the generalized estimating equations. For outcomes of VMMC safety and satisfaction among circumcised MSM, we will perform the same statistical description and comparative analyses described as above.

A 2-sided *P* value lower than .05 will be used to infer statistically significant difference. All the statistical analyses will be performed with R software (version 4.2.1; R Core Team).

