### Objectives

The primary objective of this study is to assess the efficacy of VMMC for preventing HIV acquisition among MSM who primarily engage in insertive anal sex. The secondary objectives are to assess (1) the safety of and satisfaction with surgical VMMC among MSM; (2) changes in reported sexual risk behaviors after circumcision among MSM; and (3) the efficacy of VMMC for preventing sexually transmitted infections (STIs), including herpes simplex virus type 2 (HSV-2), syphilis, and penile HPV among MSM. Our hypothesis is that VMMC could reduce the risk of HIV infection among MSM.

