### Study Measures

The baseline and follow-up surveys will collect information on sociodemographic characteristics (including age, ethnic, educational background, marital status, and monthly individual income) and sexual behaviors (including the number of male and female sex partners, frequency of vaginal or anal sex, condom use, and HIV-positive sex partners) for all enrollment participants. Follow-up surveys will be completed at 6- and 12-month follow-ups. Men randomized to receive VMMC will also be asked to complete weekly follow-up surveys for 6 weeks after VMMC to monitor for postsurgical complications, including pain, poor surgical site wound healing or infection, and premature resumption of sexual behaviors. If an adverse event is reported, trained investigators will contact participants and provide advice on whether further clinical evaluation is needed.

Fingertip blood drop samples will be collected at baseline as well as 3-, 6-, 9- and 12-month follow-ups and tested for HIV using an HIV rapid test. Venous blood samples collected at baseline as well as 6- and 12-month follow-ups will be tested for HIV, syphilis, and HSV-2. Penile swab samples will be collected at baseline as well as 6- and 12-month follow-ups and tested for HPV.

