### Limitations

The CoM Study will have several limitations. First, because the 8 study sites are located in different parts of Mainland China, we cannot ensure that VMMC will be performed in a uniform manner for all men randomized to the intervention group. We will provide men in the intervention group with a list of hospitals that provide standard VMMC services. But men will be able to choose a hospital at their own discretion. Second, MSM who undergo VMMC may experience surgical site complications, particularly when they resume insertive anal sex. Men who have recently undergone VMMC may therefore chose to avoid insertive anal sex. This may increase their frequency of receptive anal sex, and thereby, increase their risk of HIV infection. At enrollment, participants will be provided with detailed sexual health consultations to reduce sexual intercourse during abstinence. Third, sexual health behaviors will be assessed by self-report, and therefore, may be affected by recall and social desirability biases.

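### The primary Poisson model adjusts for sexual behaviors without restricting them to pre-randomization values, so its rate ratio may not be the effect of assignment to VMMC

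*Protocol article*

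**What the plan says.** The Statistical Analysis section opens with the principle: "All data will be analyzed based on the principle of intention to treat". It then treats HIV status as grouped censored data and takes the arm difference from a Poisson regression that "includes observed covariates (ie, HIV risk behaviors, such as condom use, number of sexual partners, frequency of insertive anal sex", with HIV-positive partners and "demographic variables, such as age, education level, and income" added. No time point is attached to any covariate, and the analyses are to be repeated at the 6- and 12-month visits. The paragraph before it does use the word baseline. It compares key baseline characteristics between arms and adds: "if not, subsequent analyses will assess whether these characteristics are confounding factors of the intervention".

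Four other places bear on this.
- **Study Measures:** "The baseline and follow-up surveys will collect information on sociodemographic characteristics", and the same sentence covers the sexual behaviors. Follow-up surveys fall at months 6 and 12.
- **Objectives:** a secondary aim is to assess "changes in reported sexual risk behaviors after circumcision among MSM". The Statistical Analysis section assigns this to generalized estimating equations (GEE).
- **Limitations:** "Men who have recently undergone VMMC may therefore chose to avoid insertive anal sex". The text goes on to say that receptive sex, and with it HIV risk, may rise as a result.
- **Randomization and Follow-Up:** "Randomization lists for each study site have been pregenerated by researchers", with 1:1 allocation. Site is not among the named covariates.

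**The concern.** Intention to treat asks what assignment to VMMC does to HIV incidence by every route, including any change in behavior that surgery brings about. A model that holds follow-up behavior fixed answers a different question: the rate ratio between men whose later behavior was the same. It also conditions on something that happened after randomization, so the arms compared are no longer the randomized arms.

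The protocol itself says these behaviors may change because of VMMC, yet its primary model admits them without a time limit. If circumcised men took more risk, adjustment would hide that cost and make VMMC look more protective than assignment to it was. If they took less risk, adjustment would hide a benefit.

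Two further features weaken the model. Few HIV infections are expected for the number of coefficients. And the balance check adds a second, data-driven route by which covariates could be chosen.

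**Working it through.** **1. When the covariates are measured.** Condom use, partner number, insertive frequency and HIV-positive partners exist as baseline, month-6 and month-12 values. The model is repeated at the two follow-up visits. The balance check is tied to baseline and the model covariates are not. Both readings, baseline and follow-up, are therefore open.

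**2. Whether baseline means before randomization.** Under Randomization and Follow-Up, control men complete the baseline survey after enrollment. The footnote to Table 2 counts intervention men as formally enrolled only once circumcision is complete, whereas Randomization and Follow-Up counts the time to surgery from enrollment. Table 2 places arm assignment and the baseline questionnaire in the same column without an order, and participants are not blinded. A survey taken at formal enrollment would follow randomization, and in one arm might follow surgery. The passages need to be reconciled.

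**3. Planning figure.** The point disputes no stated number, but the event count below rests on the sample size, so that was reproduced first. With rates of 10 and 2 per 100 person-years, 1-sided α of 0.10 and 80% power, the log rate-ratio formula gives (1.2816 + 0.8416)² × (1/0.10 + 1/0.02) / (ln 0.2)² = 104.4, so 105 per arm. Then 105/0.9 = 116.7, so 117 per arm or 234 in total, within 3% of the stated 240.

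**4. Events per coefficient.** After 10% loss, 120 × 0.9 = 108 per arm. With one year of follow-up each:
- Control: 108 × 0.10 = 10.8. VMMC: 108 × 0.02 = 2.16. Total: 12.96, about 13.
- Slopes: 1 for arm + 4 behaviors + 3 demographics = 8 at minimum (one term each).
- 12.96/8 = 1.6 events per slope. With no loss, (12 + 2.4)/8 = 1.8.
- Adding 7 site indicators would give 15 slopes and 12.96/15 = 0.9.

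**5. Effect of adjusting for a changed behavior (illustration; all inputs except the 0.20 are assumptions).** Let VMMC have rate ratio 0.20 at fixed behavior. Let 30% of controls have a risk behavior with its own rate ratio r, and let VMMC change that prevalence by d. Then

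total rate ratio = 0.20 × [(0.30 + d)r + 0.70 − d] / [0.30r + 0.70].

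| d | r = 1.5 | r = 3 |
|---|---|---|
| −0.10 | 0.191 | 0.175 |
| 0 | 0.200 | 0.200 |
| +0.10 | 0.209 | 0.225 |
| +0.20 | 0.217 | 0.250 |

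The model adjusted for follow-up behavior returns about 0.20 in every row. A large-sample Poisson fit at d = +0.20 and r = 3 gave 0.246 unadjusted and 0.197 adjusted. With values truly recorded before randomization, adjustment causes no such shift.

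**6. Site.** With assumed site rates of 3 to 17 per 100 person-years and 1:1 allocation within site, the simulated rate ratio was 0.198 with or without site. The type I error without site was 0.051 at nominal 2-sided 0.05.

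**The case against.** The strongest reply is that the text never says follow-up values will be used. The same items are collected at baseline, adjustment for true baseline values is legitimate, and a condensed article may leave measurement times to an analysis plan that is not shown. This stands against any claim that the model certainly adjusts for consequences of treatment. It does not remove the point, because the article does state the model and its covariates, and that wording admits follow-up values.

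A reader might infer more than the documents support:
- **That the reported ratio is not the effect of assignment.** This follows only if post-randomization values enter. The size in step 5 is assumption throughout, and the sign can go either way. The harm described under Limitations runs through receptive sex, whereas the list names insertive frequency, so even follow-up adjustment might not remove that whole pathway.
- **That leaving out site biases the ratio.** It does not, under a log link with 1:1 allocation within site. The covariate list is also open-ended, so site is not shown to be excluded. The incidences cited under Sample Size do not show differences between the trial's sites: two come from Shenyang, which is not a study city, and one is pooled over 8 cities.
- **That sparse events destroy the treatment estimate.** In simulated trials of this size the arm coefficient failed in about 12%. That matches the chance of no infections in the VMMC arm, exp(−2.16) = 0.115, which would defeat an unadjusted Poisson fit too. The instability falls on the covariate coefficients.
- **That balance tests rebuild the primary model.** The sentence promises only to assess confounding in later analyses. The objection is to leaving that door open.

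**Conclusion.** The concern holds in a limited form. As written, the primary model permits adjustment for behaviors that the protocol itself regards as possible consequences of VMMC, which conflicts with its intention-to-treat principle. Whether this will happen is not stated. If it does, the rate ratio becomes conditional on behavior. In the illustration, a total effect of 0.175 to 0.25 would be reported as about 0.20, but those limits depend on assumed prevalences and risk ratios. Restricting the covariates to baseline would not fully settle it, because that survey is not clearly pre-randomization in either arm.

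The sparsity is firmer. It rests only on the protocol's planning rates, one year of follow-up and 10% loss: about 13 events for at least 8 slopes. Stratifying by site is a matter of consistency with the randomization and corrects no bias.

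**What to change.** - **Primary comparison:** use treatment arm only, stratified by the site lists that governed randomization. A conditional analysis does this without seven site indicators: given the events in each site, the number in the VMMC arm is binomial, with a probability set by the rate ratio and the two arms' person-time there.
- **Covariate model:** move it to a sensitivity analysis restricted to values recorded before randomization. Check the dates of the baseline surveys against the randomization dates. The screening questionnaire is a possible source, but the article does not say that it records condom use or HIV-positive partners. A behavior with no pre-randomization value should be left out.
- **Balance tests:** state that they do not decide the adjustment set.
- **Follow-up behaviors:** analyze them only as outcomes in the GEE.
- **Timing:** reconcile the Table 2 footnote with Randomization and Follow-Up, so that the order of randomization, survey and enrollment is stated for each arm.

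The cost is analysis wording plus a check of dates. A little precision from strong baseline predictors is given up in the primary model. Recruitment closed in July 2022, so no new pre-randomization data can be collected, and the sensitivity model may have to be smaller than the list now named.
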